### Supervision intervention and comparator

The second experiment will evaluate the role of video-based feedback for developing therapeutic competencies and is based on the concept of competency-based supervision [22]. In the experimental group, participants (i.e., student supervisees) will show their video on behavioral activation (video 1) and cognitive (video 2) techniques of an interaction with an SP demonstrating a depressive disorder to a supervisor. Thus, supervision will be behaviorally based (direct supervision) [30]. In the control group, participants will report their experiences with the two role-plays to a supervisor; thus, the supervision will be verbally based (supervision as usual) [31].

### Duration

Each of the role-plays will last 20 min. Including the pre- and post-measurement, the first appointment will continue for 3.5 h, and the follow-up appointment will last about an hour. Training and supervision interventions are currently not standard elements of clinical psychology courses at German universities but extend beyond the established topics and didactics.

### Supervisors

The supervisors will be licensed psychotherapists (cognitive behavioral therapy). They will be provided with a supervision manual based on Falender and Shafranske [22] and Hautzinger [26]. Supervisors are intended to be recruited from an internal database of former study supervisors. In advance of the first supervision session, they will receive a 10-h training session in order to standardize supervision. Supervisors will not be part of the study team (i.e., they will be external). One supervision session will last 30 min, and each supervisor will receive €50.

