## Methods/Design

### Study design

The study is a single-center RCT (see Fig. 1) in which participants (i.e., bachelor’s and master’s students included as either trainees or supervisees) will conduct therapy sessions with SPs. All sessions will be video-recorded. Following a preparation period, both experiments will be conducted consecutively within a 2-year period. Data will be gathered before and after training/supervision and at the 3-month follow-up. Participants fulfilling the inclusion criteria (see below) will be randomly assigned by computer-generated numbers in a 1:1 ratio and allocated to the experimental or control groups and to the order of the training topics (behavioral activation and cognitive strategies or vice versa). The allocation will be implemented by a researcher (who is independent of the role-plays). The researcher will enroll and assign participants and provide sealed envelopes containing the study material. To reduce the possibility for unblinding, the researcher and student assistants will urge all participants not to speak to any other students about the trial.

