### Secondary outcomes

Therapeutic alliance and the participant empathy will be evaluated by the raters, participants, and SPs. We will use the Helping Alliance Questionnaire [40], or its German version [41], and the Empathy Scale [42], which will be adapted to the three perspectives.

For measuring therapeutic adherence, we will use the Cognitive Behavioral Therapy Adherence Scale (CBT-AS) [43]. The CBT-AS will be adapted for the topics of behavioral activation and of cognitive biases based on the depression manual used [26].

The therapeutic knowledge of participants will be evaluated by MCQs and case vignettes [5]. The materials will be self-developed in accordance with the above-mentioned manual [26] and recommendations for the construction of MCQs [43].

Further outcomes taken into consideration will be the participant’s personality (Big Five Inventory, or BFI-K) [44], state–trait anxiety (State–Trait Anxiety Inventory) [45], and individual perception of the study adapted from [46, 47].

The raters will evaluate the SP’s authenticity ([name], [name], [name]: Can simulated patient encounters appear authentic? Development and pilot results of an observer-based rating instrument, submitted), and the SPs will evaluate the participant’s counseling skills [42, 48].

Negative therapist effects will be assessed by items adapted from published German questionnaires [49, 50]. Furthermore, possible allegiance effects of supervisors will be captured by a questionnaire adapted to supervision [51].

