### Statistical analysis and power calculation

To avoid attrition bias, we will include all randomly assigned participants in the primary analyses (intention-to-treat). Second, we will perform per-protocol analyses and compare the results with those from the intention-to-treat analyses. We will use chi-squared tests for nominal data and analyses of variance/analyses of covariance (ANOVAs/ANCOVAs) for ordinal and interval data. For the analysis of training/supervision effects, the ANOVAs will involve a group factor (training/supervision condition) and a time factor (before, after, and follow-up). Possible pre-differences between the groups will be taken into account via the ANCOVAs. The α level will be set at 0.05 and Bonferroni-corrected for multiple testing. Missing data will be addressed according to the outcome and data structure (e.g., complete case analyses and imputation by expectation-maximization or by last observation carried forward).

Considering prior studies [24, 52], we assume moderate competence differences between the groups (Cohens *d* = 0.60) and high correlations between competence ratings (*r* = 0.50). Given an *α* of 0.05 and a 1-*β* of 0.80 (power), a sample of 68 participants will be necessary in each experiment, resulting in an overall sample size of 136 (G*Power Version 3.1.9.2) [53].

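### Experiment 2: the stated analysis and the N of 68 treat supervisees as independent, and no stated rule balances supervisors over the two conditions

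*Protocol article*

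**What the plan says.** All references are to the protocol article.

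- **Supervisors.** They are external licensed psychotherapists who receive a manual and 10 hours of training; a session lasts 30 minutes. On their source: "Supervisors are intended to be recruited from an internal database of former study supervisors". Neither their number nor their caseload is given.
- **Supervision intervention and comparator.** In each arm the participant meets a supervisor. Whether one supervisor works in one arm or in both is not said.
- **Study design.** Participants are "randomly assigned by computer-generated numbers in a 1:1 ratio and allocated to the experimental or control groups and to the order of the training topics". Supervisor is not among the things allocated.
- **Statistical analysis and power calculation.** For training and supervision effects, "the ANOVAs will involve a group factor (training/supervision condition) and a time factor (before, after, and follow-up". ANCOVAs handle baseline differences. No supervisor term appears. On size: "a sample of 68 participants will be necessary in each experiment, resulting in an overall sample size of 136".
- **Secondary outcomes.** "possible allegiance effects of supervisors will be captured by a questionnaire adapted to supervision". No analysis that uses this score is described.

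**The concern.** Participants who share a supervisor share that person's skill and enthusiasm, so their competence scores may be correlated. Neither the stated model nor the sample size allows for this.

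Two things are at stake. If a supervisor works in one condition only, the video-versus-verbal contrast in hypotheses 3 and 4 cannot be separated from who supervised, and the standard error is too small. If supervisors work in both conditions but are not modelled, their variance stays in the error term and costs a little power. The first problem has to be prevented when supervisors are scheduled, because no later model term fully repairs it.

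The article does not state that supervisors see several participants, but two details point that way:

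- One supervisor per participant, even with a single session each, would mean 68 × 10 h = 680 h of training for 68 × 0.5 h = 34 h of supervision.
- The payment sentence for supervisors has the same form as the one for raters. Two raters assess three role-plays per student, that is 68 × 3 = 204 role-plays or about 102 h each per experiment at 30 minutes. Their €20 can sensibly only be per assessment. Read the same way, the supervisors' €50 is per session, which suggests repeated sessions.

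**Working it through.** **Inputs from the article:** d = 0.60, so f = d/2 = 0.30; r = 0.50; α = 0.05 (taken as two-sided); power 0.80; N = 68, 34 per arm. The r concerns "high correlations between competence ratings", which is read here as repeated ratings of the same participant and not as a supervisor ICC. The Bonferroni divisor is not given, so α stays at 0.05 as in the article's own calculation.

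**Assumed, because the article gives neither:** k supervisors per arm (or in total, if crossed) and the supervisor ICC.

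**1. The stated N.** For the between-groups effect in a repeated-measures ANOVA with m measurements, λ = f²·N·m / [1 + (m − 1)r]. With m = 2, λ = 0.09 × 68 × 2 / 1.5 = 8.16. On 1 and 66 degrees of freedom this gives power 0.804, and 68 is the smallest even N that reaches 0.80. Other forms give similar numbers: m = 3 gives 62 and an ANCOVA gives 33 per arm. All of them assume independent participants.

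**2. Supervisors nested in arms: size of the effect.** The caseload is n = 34/k and the design effect is DE = 1 + (n − 1)·ICC. For k = 3 and ICC 0.05, n = 11.33 and DE = 1 + 10.33 × 0.05 = 1.52. The N needed is 68 × 1.517 = 103.1, so 104 at the same caseload, which means more supervisors. At N = 68, λ falls to 8.16 / 1.517 = 5.38 and power to 0.63. With degrees of freedom for supervisors, 2(k − 1) = 4, power is 0.43.

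| k per arm | ICC | DE | N needed | power at 68 | power, df = 2(k − 1) |
|---|---|---|---|---|---|
| 3 | 0.05 | 1.52 | 104 | 0.63 | 0.43 |
| 3 | 0.10 | 2.03 | 139 | 0.51 | 0.34 |
| 6 | 0.05 | 1.23 | 84 | 0.72 | 0.64 |
| 6 | 0.10 | 1.47 | 100 | 0.64 | 0.57 |

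**3. Supervisors nested: type I error if they are ignored.** Simulated two-sample test at 5%, 10,000 trials per setting:

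| k per arm | ICC 0.02 | ICC 0.05 | ICC 0.10 |
|---|---|---|---|
| 3 | 7.4% | 11.4% | 17.6% |
| 6 | 6.4% | 7.9% | 10.5% |

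A separate simulation of 20,000 trials gave 10.9% and 16.8% for k = 3, and 7.9% and 10.8% for k = 6, at ICC 0.05 and 0.10. A hand check for k = 3 and ICC 0.05: the critical t on 66 df is 1.997, and 1.997/√1.517 = 1.62, whose two-sided tail is about 11%. At the mild end, 8 per arm with ICC 0.01 gives 5.6% error and power 0.79.

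**4. Supervisors crossed with condition, balanced, not modelled.** The supervisor main effect cancels from the contrast but stays in the error variance. With 6 supervisors in total, type I error is 4.7%, 4.3% and 4.0% at ICC 0.02, 0.05 and 0.10. With 3 or 5 supervisors it is 3.8 to 4.5% at ICC 0.05 and 0.10. These runs assume that the method effect does not vary between supervisors. Under crossing, adding supervisor as a factor restores the nominal level with equal or slightly higher power.

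**The case against.** The strongest reply is that the harm rests on a branch that the article never states. It describes one pool of supervisors with one manual and one training, which fits crossing at least as well as nesting, and under balanced crossing the error is not inflated. A reader might infer that a few supervisors each serve one arm and that this trial therefore runs at 11 or 18% error. The documents do not support that: they give no supervisor number, no caseload and no nesting. This part of the reply stands.

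A second reply is that an article leaves rosters to the full protocol and supervisor effects to the analysis plan, neither of which is shown. The sentence on the ANOVAs covers both experiments and does not say that group and time are the only terms. This stands in part. The full documents may settle the matter. Even so, the article does commit itself to a model, an N and a list of what is allocated, and none of the three allows for supervisors.

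Third, a reader might infer that unblinded supervisors can bias the scoring. They cannot do so directly: the primary outcome is scored by two independent external raters blinded to condition, with a check on unblinding, and the simulated patients are blinded too. Supervisor enthusiasm can act only through how supervision is delivered. The manual and training may also hold the ICC down, but the article gives no figure for it.

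Finally, crossing does not remove allegiance. A supervisor who favours video may deliver the verbal format less well, and one person delivering both may blend them. This is correct and shapes the fix.

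**Conclusion.** The point holds in a conditional form. The stated analysis and sample size ignore a probable source of correlation, and the rule that decides whether this matters is not stated. With nesting, type I error would be about 6 to 18% for 3 to 6 supervisors per arm and an ICC of 0.02 to 0.10, and method and supervisor could not be separated. With balanced crossing and a method effect that is constant over supervisors, the planned test is valid and loses only a little. Supervisor number and ICC are assumptions, so none of the inflated rates is an established property of this trial. The point is still worth acting on: it concerns the main contrast of the second experiment, and the remedy is cheap. Only hypotheses 3 and 4 are affected.

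**What to change.** - State the number of supervisors and the planned caseload.
- Have each supervisor deliver both conditions in about equal numbers, by blocking the randomisation of condition within supervisor.
- Include supervisor as a factor in the model for hypotheses 3 and 4.
- Report a sensitivity analysis with a supervisor-by-condition term and the allegiance score already collected, because crossing alone does not deal with allegiance.
- If supervisors have to be nested in arms, use a random supervisor effect with small-sample degrees of freedom, and restate the power under a stated ICC.

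The cost is a scheduling constraint, a few degrees of freedom, and some risk that supervisors mix the two formats. The manual and the 10-hour training are the obvious place to address that risk, but the article does not show that they would prevent it. No extra supervisors are needed for the crossed design. The experiments run consecutively, so the rule can be set before the second one starts.

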### Raters

The two raters will be licensed psychotherapists or therapists-in-training (cognitive behavioral therapy) and are also intended to be recruited from an internal database of former raters. In advance of the first session, they will receive 10 h of training on the use of the instruments for the assessment of the video-recorded interactions. Raters will not be part of the study team and will conduct their ratings independently of each other. They will be blinded to the experimental conditions. As a manipulation check, they will be asked at the end of each rating whether they can identify the condition (experimental versus control). One assessment will take around 30 min, and each rater will receive €20.

### Primary outcome

Psychotherapeutic competencies serve as the primary outcome. They will be assessed by trained raters (see above) via the German adaptation [32, 33] of the Cognitive Therapy Scale [34]. Therapeutic techniques will be assessed by the raters using a self-developed therapeutic skills checklist based on published instruments [35–39] and adapted to the psychotherapy field.

### Secondary outcomes

Therapeutic alliance and the participant empathy will be evaluated by the raters, participants, and SPs. We will use the Helping Alliance Questionnaire [40], or its German version [41], and the Empathy Scale [42], which will be adapted to the three perspectives.

For measuring therapeutic adherence, we will use the Cognitive Behavioral Therapy Adherence Scale (CBT-AS) [43]. The CBT-AS will be adapted for the topics of behavioral activation and of cognitive biases based on the depression manual used [26].

The therapeutic knowledge of participants will be evaluated by MCQs and case vignettes [5]. The materials will be self-developed in accordance with the above-mentioned manual [26] and recommendations for the construction of MCQs [43].

Further outcomes taken into consideration will be the participant’s personality (Big Five Inventory, or BFI-K) [44], state–trait anxiety (State–Trait Anxiety Inventory) [45], and individual perception of the study adapted from [46, 47].

The raters will evaluate the SP’s authenticity ([name], [name], [name]: Can simulated patient encounters appear authentic? Development and pilot results of an observer-based rating instrument, submitted), and the SPs will evaluate the participant’s counseling skills [42, 48].

Negative therapist effects will be assessed by items adapted from published German questionnaires [49, 50]. Furthermore, possible allegiance effects of supervisors will be captured by a questionnaire adapted to supervision [51].

### Statistical analysis and power calculation

To avoid attrition bias, we will include all randomly assigned participants in the primary analyses (intention-to-treat). Second, we will perform per-protocol analyses and compare the results with those from the intention-to-treat analyses. We will use chi-squared tests for nominal data and analyses of variance/analyses of covariance (ANOVAs/ANCOVAs) for ordinal and interval data. For the analysis of training/supervision effects, the ANOVAs will involve a group factor (training/supervision condition) and a time factor (before, after, and follow-up). Possible pre-differences between the groups will be taken into account via the ANCOVAs. The α level will be set at 0.05 and Bonferroni-corrected for multiple testing. Missing data will be addressed according to the outcome and data structure (e.g., complete case analyses and imputation by expectation-maximization or by last observation carried forward).

Considering prior studies [24, 52], we assume moderate competence differences between the groups (Cohens *d* = 0.60) and high correlations between competence ratings (*r* = 0.50). Given an *α* of 0.05 and a 1-*β* of 0.80 (power), a sample of 68 participants will be necessary in each experiment, resulting in an overall sample size of 136 (G*Power Version 3.1.9.2) [53].

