### Objectives and hypotheses

Therefore, the aim of this study is to use SPs to evaluate specific training and supervision conditions. Psychology students will be taught distinct interventions relevant for the cognitive behavioral therapy of patients with diagnosed depression (i.e., behavioral activation and cognitive interventions based on an established treatment manual) [26]. The focus on depression was chosen because, on the one hand, it is one of the most prevalent mental disorders [27] and, on the other hand, psychotherapeutic competencies are highly relevant for depression treatment [28, 29].

The study combines the development of SP methods with two consecutive experiments. During the developmental phase, scenarios for the SP portrayals will be developed and validated, instruments for the assessment of therapist behavior and SP authenticity will be developed, SPs will be recruited and trained thoroughly, and their portrayal will be validated on the basis of video recordings.

In the first experiment, two specific training strategies (i.e., reading written instructions with or without modeling) will be compared. In the second experiment, two central supervision techniques (i.e., based on treatment videos versus on verbal reporting) will be evaluated. We expect post-training, psychology students randomly assigned to the active strategy of modeling to display more therapeutic competencies than students who were only reading the written instructions on behavioral activation or cognitive techniques (hypothesis 1). Furthermore, we expect the competence differences between the two groups to persist until the 3-month follow-up (hypothesis 2). Second, we expect that post-supervision, psychology students randomly assigned to supervision based on treatment videos will display more therapeutic competencies than the students who described their treatment verbally to the supervisor (hypothesis 3). Again, we expect the competence differences between the two groups to persist at the 3-month follow-up (hypothesis 4).

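### The baseline-adjusted comparison that delivers the stated 80% power at N = 68 is not fixed as the primary test; the group × time ANOVA described has about 72% and does not isolate the differences in hypotheses 1–4

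*Protocol article*

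**What the plan says.** All analysis statements are in the protocol article, section Statistical analysis and power calculation. For training and supervision effects, "the ANOVAs will involve a group factor (training/supervision condition) and a time factor (before, after, and follow-up"), so the baseline role-play is one level of the outcome. The next sentence is the only one that gives ANCOVA a purpose: "Possible pre-differences between the groups will be taken into account via the ANCOVAs". On multiplicity: "The α level will be set at 0.05 and Bonferroni-corrected for multiple testing".

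The sample size rests on two assumptions: "we assume moderate competence differences between the groups (Cohens *d* = 0.60") and "high correlations between competence ratings (*r* = 0.50"). From these, "Given an *α* of 0.05 and a 1-*β* of 0.80 (power), a sample of 68 participants will be necessary in each experiment". The test behind that calculation is not named.

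Under Objectives and hypotheses, hypotheses 1 and 3 concern the group difference right after training or supervision, and hypotheses 2 and 4 the difference at 3 months. For supervision, the latter reads: "Again, we expect the competence differences between the two groups to persist at the 3-month follow-up (hypothesis 4").

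**The concern.** Each hypothesis is a difference between two randomised groups at one named time. A group × time ANOVA over three times does not give that difference directly. Its interaction term, the usual test of an intervention effect in a before/after/follow-up design, has 2 degrees of freedom and responds to any divergence of the two profiles. A significant result does not say whether the groups differ at post, at 3 months or both.

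The baseline score is most useful as a covariate, because its correlation with the later score removes residual variance. That gain is the same whether or not the groups happen to differ at baseline. Linking ANCOVA to possible pre-differences leaves it unclear whether the adjusted comparison is the primary test. At stake are the power claimed for N = 68 and a direct answer to all four hypotheses.

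**Working it through.** **Inputs from the protocol article.** d = 0.60 (f = 0.30), r = 0.50, α = 0.05, power 0.80, N = 68 per experiment (section Statistical analysis and power calculation); 1:1 allocation, so 34 per group (section Study design).

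**Assumptions added.** F tests, equivalent to two-sided testing; SD 1 at each time; the same correlation r between all pairs of times (compound symmetry); true group differences of 0 at baseline (randomisation), 0.60 at post and 0.60 at follow-up (full persistence, as hypotheses 2 and 4 expect). No Bonferroni correction unless stated. λ is the noncentrality parameter of the F distribution.

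**Step 1: reproduce N = 68.** Smallest even N reaching 80% power:

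| Test | λ | N |
|---|---|---|
| ANCOVA of one later score on group and baseline | (N/4)·d²/(1 − r²) = 0.12·N | 68 (power 0.803) |
| Repeated measures, between factor, 2 measurements | f²·N·2/(1 + r) = 0.12·N | 68 (0.804) |
| Repeated measures, between factor, 3 measurements | f²·N·3/(1 + 2r) = 0.135·N | 62 (0.812) |
| Within–between interaction with f = 0.30, 2 or 3 measurements | f²·N·m/(1 − r), m = number of measurements | 24 or 20 |
| Two-sided t-test at post, no baseline | (N/4)·d² = 0.09·N | 90 |

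N = 68 is therefore correct arithmetic for two tests with the same λ of 0.12 × 68 = 8.16. Of the rows above, none with a three-level time factor gives 68.

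**Step 2: power of the group × time interaction at N = 68.** The mean of the differences (0, 0.6, 0.6) is 0.4. Squared deviations: 0.16 + 0.04 + 0.04 = 0.24.

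λ = (N/4) × 0.24/(1 − r) = 17 × 0.24/0.50 = 8.16, df = (2, 132), power 0.716. A simulation of 20,000 trials gave 0.717. Reaching 80% with this test needs N = 82.

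**Step 3: power of the baseline-adjusted ANCOVA at N = 68.**

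λ = 17 × 0.36/(1 − 0.25) = 8.16, df = (1, 65), power 0.803. Simulation gave 0.792. The same holds for the follow-up score if d = 0.60 persists. At r = 0.50 the two λ values coincide; the ANCOVA gains because it spends one numerator degree of freedom instead of two.

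**Step 4: sensitivity to r.**

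| r | Interaction λ = 4.08/(1 − r) | Power | ANCOVA λ = 6.12/(1 − r²) | Power |
|---|---|---|---|---|
| 0.3 | 5.83 | 56% | 6.73 | 72% |
| 0.5 | 8.16 | 72% | 8.16 | 80% |
| 0.7 | 13.60 | 91% | 12.00 | 93% |

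**Step 5: sensitivity to persistence and α.** If the follow-up difference falls to 0.30, the interaction has 58% power at r = 0.50; the ANCOVA at post is unaffected. If Bonferroni covers two tests per experiment (an assumption, as the number is not given; α = 0.025), the interaction has 61% and the ANCOVA 71%.

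**The case against.** The strongest reply is that ANCOVA is already planned. The sentence says plainly that it will be used, the section names ANOVAs and ANCOVAs together, and N = 68 is what a baseline-adjusted ANCOVA needs. This has weight. The sentence can be read as planning ANCOVA in any case, but it does not make it primary or say which score it is applied to. The match at 68 does not settle the intention either, because a two-measurement between-group test gives the same number.

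A second reply is that the choice of ANOVA term or follow-up contrast for each hypothesis is commonly left to an analysis plan, which is not shown. That is fair, and the missing contrast is not the point by itself. The point is that the article does describe an effect analysis, and the power it states belongs to another test.

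Four stronger readings are tempting but not supported:

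- *Adjustment is triggered by observed imbalance.* The article gives no baseline test, threshold or condition.
- *The unadjusted ANOVA is the declared main analysis.* ANOVA and ANCOVA are described in consecutive sentences and neither is ranked.
- *The trial has only 51% power.* That is the group main effect averaged over all three times: λ = 17 × 0.4²/(2/3) = 4.08, df = (1, 66). The article nominates this term for no hypothesis.
- *Persistence will be inferred from a non-significant change between post and follow-up.* No such inference is planned; hypotheses 2 and 4 already read as group differences at follow-up.

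**Conclusion.** The point holds as one of efficiency and targeting. Under the protocol's own inputs, the group × time interaction has about 72% power at N = 68, against 80% for a baseline-adjusted ANCOVA, and it does not isolate the post or the 3-month difference. The stated 80% is delivered by the ANCOVA, which is not fixed as the primary test.

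The size of the gap rests on compound symmetry, full persistence of d = 0.60, r = 0.50 and α = 0.05 before Bonferroni. It is 16 percentage points at r = 0.3 (72% against 56%) and about 1 at r = 0.7. At high correlation the power argument nearly vanishes, and what remains is that an omnibus test does not answer a hypothesis about one time.

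The sample size is not arithmetically wrong. The ANOVA is valid under randomisation, so there is no bias and no inflated type I error. A wording correction settles the matter.

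**What to change.** In the section Statistical analysis and power calculation:

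1. Make the primary test of hypotheses 1 and 3 an ANCOVA of the post competence score on group, adjusted for the baseline competence score whether or not the groups differ at baseline.
2. Test hypotheses 2 and 4 in the same way on the 3-month score. Alternatively, fit one mixed model to the post and follow-up scores with baseline as covariate, and read the group contrast at each time.
3. State that the 80% power at N = 68 refers to this test at α = 0.05, before Bonferroni correction.

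The three-time ANOVA can stay as a supporting description of the profiles. The cost is a few sentences: baseline competence is already rated for every participant, and neither the sample size nor the data collection changes. Adjusting for degree level (bachelor's or master's) would be an optional refinement and is not part of this point.

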**Methods:**

In this study, standardized role-plays are used to evaluate methods for training and supervision. Central cognitive behavioral approaches for treating depression are taught in the training. The first experiment compares an active training approach (i.e., model learning) with a passive one (i.e., reading manual-based instructions). The second experiment compares a direct supervision technique (i.e., supervision based on video analysis) with an indirect one (i.e., supervision based on verbal reporting). In each experiment, 68 bachelor’s and master’s students of psychology will be randomly assigned to the experimental and control groups. Each student takes part in three role-plays (baseline, post and 3-month follow-up), which are all videotaped. Two independent raters assess therapist competencies in each role-play on the basis of a standardized competence scale.

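### The sample size of 68 per experiment is powered at an uncorrected α of 0.05, while the stated testing rule is Bonferroni-corrected; if the correction covers the two hypotheses per experiment, power is about 71%, not 80%

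*Protocol article*

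**What the plan says.** All the statements about α and sample size are in the protocol article, section Statistical analysis and power calculation.

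- **Testing rule:** "The α level will be set at 0.05 and Bonferroni-corrected for multiple testing". The article does not give the number of tests, the family they belong to, or any exemption for the primary outcome.
- **Power statement:** "Given an *α* of 0.05 and a 1-*β* of 0.80 (power"), with no mention of a correction.
- **Assumptions:** "we assume moderate competence differences between the groups (Cohens *d* = 0.60") and "high correlations between competence ratings (*r* = 0.50").
- **Result:** "a sample of 68 participants will be necessary in each experiment", or 136 overall.

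The section Objectives and hypotheses gives each experiment two hypotheses on therapeutic competence. Hypotheses 1 and 3 concern the difference after training or supervision. Hypotheses 2 and 4 concern its persistence; for the first experiment, "we expect the competence differences between the two groups to persist until the 3-month follow-up".

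The Methods part of the Abstract gives 68 per experiment as the number randomised as well. The statistical section plans an intention-to-treat analysis and names complete-case analysis and imputation as possible ways of handling missing data.

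**The concern.** Two adjacent paragraphs use different significance thresholds. Read as written, the correction reaches the confirmatory tests, so the stated 80% belongs to a threshold those tests would not be judged against. If two hypotheses share the 0.05, a true effect of the assumed size is missed about 29% of the time at each test instead of about 20%. A non-significant result could then be taken as evidence against modelling or video-based supervision more readily than the design allows.

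A second, smaller issue affects only the follow-up hypotheses. The number needed for analysis equals the number randomised, so the calculation leaves no room for participants who do not return at 3 months.

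**Working it through.** **Inputs.** From the statistical section: d = 0.60, r = 0.50, α = 0.05, N = 68 per experiment. From Study design: 1:1 allocation, so 34 per arm. Sidedness and the G*Power module are not stated. I assume an F test, equivalent to a two-sided test, because ANOVA/ANCOVA is planned.

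**Step 1: reproduce the plan's figure.** For a two-group comparison adjusted for baseline, the noncentrality parameter is

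λ = N · (d/2)² / (1 − r²) = 68 · 0.09 / 0.75 = 8.16, with (1, N − 3) = (1, 65) degrees of freedom.

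- N = 68, α = 0.05: power 80.3%.
- N = 66, α = 0.05: power 79.1%.

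So 68 is the smallest balanced N that reaches 80%. A repeated-measures between-group test with two measurements also gives 68: λ = f²·N·m / (1 + (m − 1)·r) = 0.09 · 68 · 2 / 1.5 = 8.16, power 80.4%. The other models tried do not give 68: an unadjusted two-sided t test needs 90, a one-sided one 72, and the between-group test with three measurements 62. The stated size therefore contains neither a Bonferroni correction nor a dropout margin.

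**Step 2: apply the stated correction at N = 68, no loss.**

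| Tests in the family | α per test | Power | N for 80% |
|---|---|---|---|
| 1 (as powered) | 0.05 | 80.3% | 68 |
| 2 (the two hypotheses of one experiment) | 0.025 | 71.2% | 82 |
| 4 (scenario only) | 0.0125 | 61.4% | 98 |

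Under the three-measurement model, which does not reproduce 68, the last two powers would be 76.8% and 67.7%, still below 80%.

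**Step 3: follow-up loss.** The article gives no loss rate. Assuming 10% or 20% loss and complete-case analysis, 68 becomes 61 or 54, and λ becomes 7.32 or 6.48. Power for hypotheses 2 and 4 is then:

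| Assumed loss | α = 0.05 | α = 0.025 |
|---|---|---|
| 10% (N = 61) | 75.8% | 65.7% |
| 20% (N = 54) | 70.5% | 59.5% |

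**Step 4: what a fixed sequence would give.** If hypothesis 1 is tested at 0.05 and hypothesis 2 only when hypothesis 1 is significant, hypothesis 2 can be claimed only when both tests succeed. I simulated d = 0.60 at both times, all pairwise correlations 0.50 and baseline-adjusted two-sided tests. The first test has about 80% power.

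| Assumed loss at follow-up | Claiming H2 under the fixed sequence | H2 under Bonferroni at 0.025 |
|---|---|---|
| None | about 66% | about 70% |
| 10% | about 63% | about 65% |
| 20% | about 59% | about 59% |

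The simulated 70% is slightly below the 71.2% of Step 2 because the formula ignores chance baseline imbalance between the arms, and the simulation includes it.

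**The case against.** The strongest reply is that the article never says which tests the correction covers. The sentence follows a list of chi-squared tests, ANOVAs and ANCOVAs and a three-level time factor, and the article has many secondary outcomes. The authors may have meant the correction for those outcomes or for pairwise time contrasts, leaving one main test per experiment at 0.05. An analysis plan that is not shown may define the family. This stands in part: 71% is conditional on the correction covering the two hypotheses. It does not remove the point, because the article itself states both the correction and the α used for power, with no restriction that reconciles them.

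A reader might go further than the document allows in four ways.

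- **That power is 61%.** This needs a family of four. Each experiment has its own sample and question, which points to two. Reaching four through two instruments would require the skills checklist to be a co-primary measure. Primary outcome mentions it for therapeutic techniques, apart from the Cognitive Therapy Scale for competencies, so that is only one reading.
- **That no hypothesis has its stated power.** This is not established while the family is undefined.
- **That attrition undermines every test.** Under Duration, the pre- and post-measurements fall within one 3.5-hour appointment, so hypotheses 1 and 3 face little dropout. The loss rates above are assumptions. The article also lists imputation, although imputation does not restore the information in unobserved follow-up ratings.
- **That 68 was miscalculated.** It is exact for its stated inputs. The fault is a mismatch between two statements.

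**Conclusion.** The point holds as an inconsistency between the testing rule and the power statement. At the uncorrected 0.05, 68 gives 80.3% with nothing to spare. If Bonferroni covers the two hypotheses of each experiment, which is the plain reading, power is about 71% for each. About 61% for four tests is a scenario and should not be quoted as the trial's power. Neither figure includes attrition. For hypotheses 2 and 4 at α = 0.025, an assumed 10% or 20% loss analysed as complete cases gives about 66% or 60%.

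These results rest on d = 0.60, r = 0.50, equal arms, a two-sided baseline-adjusted test and, for the 71%, a family of two.

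**What to change.** State which tests the Bonferroni correction covers and make the power statement match. Two versions work without adding participants.

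1. **Keep Bonferroni over the two hypotheses in each experiment** and restate the power as about 71% per hypothesis before attrition. The cost is a less favourable stated power.
2. **Treat each experiment as its own family and test in a fixed order:** hypothesis 1 (or 3) at two-sided 0.05, then hypothesis 2 (or 4) at 0.05 only if the first is significant. Keep Bonferroni for the secondary outcomes. This controls the error rate within each experiment and keeps about 80% for hypotheses 1 and 3. The cost falls on hypotheses 2 and 4: the chance of claiming them is about 66% with no loss, slightly below the 70% under Bonferroni, and they cannot be claimed at all if the first test fails. The protocol should state this downside.

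The choice depends on whether the immediate or the lasting effect matters more. In either case, give the power for hypotheses 2 and 4 under an explicit attrition assumption. The edit is two or three sentences in the statistical section and should be made before outcome data are analysed. Trial status already provides for reporting protocol modifications.
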